Age, GP practice, diabetes status and calendar time are matching variables. Our models will also be adjusted for the following potential confounders evaluated at beginning of follow up:

- Smoking status (never-smoker, current smoker, ex-smoker)
- BMI (underweight, normal, overweight, obese)
- Alcohol status (never-drinker, current drinker, ex-drinker)
- Index of multiple deprivation score

*Interaction*

We will fit interaction terms to explore possible effect modification between exposure to a PDE5 inhibitor and age, smoking status and index of multiple deprivation score.

*Sensitivity analysis*

As a sensitivity analysis we will exclude the first 12 months of follow up after index date in both exposed and unexposed patients. This is to decrease the chance of reverse causality, whereby undiagnosed melanoma cancers cause ED and hence the need for a PDE5 inhibitor prescription.

We will also conduct an analysis restricted to patients diagnosed with diabetes as previous restrictions mean all patients diagnosed with diabetes were definitely eligible for a PDE5 prescription.

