**Limitations**

*Missing data*

Although there is known missingness in the smoking and alcohol status and BMI variables, this is minimal. Initial feasibility analyses using a CPRD random sample show that 2.3% and 1% of patients prescribed a PDE5 inhibitor have missing data for alcohol status and smoking status respectively. We plan to conduct a complete case analysis, which relies on the assumption that the probability of these data being missing is independent of melanoma risk, conditional on covariates [7]; given the small amount of missing data, any violation of the assumption is unlikely to importantly affect the results.

*Lack of data on UV Exposure*

UV exposure is a strong risk factor for malignant melanoma, though it is unclear as to whether UV exposure is likely to be associated with PDE5 inhibitor use and therefore a potential confounder. As data on patient level UV exposure are unavailable, we will match on GP practice as we believe patients from the same practice will have similar sun exposures whilst at home due to geographical location, though a limitation is that it will be impossible for us to take account of amount of time spent outdoors. We will also adjust for index of multiple deprivation score as we believe this will to some extent act as a proxy for amount of travel abroad.

*Sale of PDE5 inhibitors without a prescription*

There is a high volume of PDE5 inhibitors, especially sildenafil (marked as Viagra), sold illegally. It is therefore possible that patients could obtain medication without a prescription resulting in exposure status misclassification. If this is the case, it would result in an underestimation of the true effect size.

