**CHANGES FROM THE PROTOCOL AND EXPLANATION**

We added an extra exclusion criteria: men with no consultation in the year prior to the index date were excluded from the study. This is because we initially discovered a large discrepancy in the proportion of non-consulting patients between the exposed and unexposed groups, with the unexposed much more likely to be non-consulters, implying a potential for substantial differences in ascertainment of outcomes, and therefore bias. All analyses were otherwise carried out as pre-specified, but we conducted some further analyses to assess causality and exclude bias, as follows:

1. We added an extra secondary analysis to investigate changes in the association between PDE5 use and melanoma by time since first prescription date. This was to further explore whether patterns of effects were consistent with causality.

2. We investigated interaction by practice region, as well as by the pre-specified potential effect modifiers. This was because of an apparent important role for sun exposure; the climate in the southern UK is generally warmer with more hours of sunshine than in the northern part of the country.

3. We added three negative control outcomes (basal cell carcinoma, solar keratosis, colorectal cancer) as a way of excluding bias. No causal effects of PDE5 inhibitor use were postulated for these outcomes. The specific outcomes were chosen to incorporate one non-melanoma skin malignancy, one non-malignant skin condition, and one condition unrelated to skin.

4. We conducted a post-hoc analysis to relate PDE5 exposure to prior solar keratosis, in order to assess possible confounding by sun exposure.

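### Residual UV confounding of the melanoma hazard ratio is possible, and no described melanoma model uses prior solar keratosis, the patient-level sun-exposure proxy already in hand, to gauge it

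*Combined protocol and SAP*

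**What the plan says.** The protocol's Limitations section treats UV as a strong risk factor for melanoma but leaves its role as a confounder open: "it is unclear as to whether UV exposure is likely to be associated with PDE5 inhibitor use and therefore a potential confounder". It then gives the planned handling: "As data on patient level UV exposure are unavailable, we will match on GP practice". Deprivation score is added as a partial proxy for foreign travel. The same paragraph admits that time spent outdoors cannot be taken into account.

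The Confounding subsection of the analysis plan gives the model. On the design side, "Age, GP practice, diabetes status and calendar time are matching variables", and the Cox model is stratified by matched set. On the covariate side, "Our models will also be adjusted for the following potential confounders evaluated at beginning of follow up", followed by smoking, BMI, alcohol and deprivation score. No skin or sun marker is listed.

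The closing section, on changes from the protocol, reports an extra exclusion (men with no consultation in the year before index) and states "All analyses were otherwise carried out as pre-specified". It then lists four further analyses. Solar keratosis appears in two of them. Item 3 uses it as an outcome: "We added three negative control outcomes (basal cell carcinoma, solar keratosis, colorectal cancer) as a way of excluding bias". Item 4 uses it as a prior condition: "We conducted a post-hoc analysis to relate PDE5 exposure to prior solar keratosis, in order to assess possible confounding by sun exposure". The result of item 4 is not given.

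**The concern.** Item 4 could not have been run without a patient-level record of prior solar keratosis, and the investigators themselves treat it as a marker of sun exposure. If it is measured before the index date it cannot be a consequence of PDE5 use, so it is a legitimate candidate covariate. Relating it to exposure can signal that confounding may be present. It does not show how far the melanoma hazard ratio moves when the marker is taken into account, which is what a reader needs to know.

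The other safeguards do not answer that question either. Practice matching controls location, while time outdoors and holidays vary within a practice. Deprivation score is offered only as a partial proxy. Interaction by region tests effect modification, not confounding within practices. Negative control outcomes can signal bias but leave the melanoma estimate unchanged.

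What is at stake is the reading of a modest hazard ratio. The sample size section puts the detectable effect at about 1.18, and an uncontrolled imbalance in sun exposure could in principle contribute to an estimate of that size.

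**Working it through.** **1. The yardstick of 1.18.** Inputs from the sample size section: 179,298 exposed men, melanoma in about 0.27%, one control each, 5% significance, 80% power. This gives 179,298 × 0.0027 ≈ 484 melanomas in the exposed.

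Take 0.27% as the exposed risk. The control risk is then 0.0027/1.18 = 0.002288, the difference 0.000412 and the pooled risk 0.002494. The standard error is √(2 × 0.002494 × 0.9975/179,298) = 0.0001666, so the standardised difference is 2.472.

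- One-sided 5%: Φ(2.472 − 1.645) = 79.6%, which matches the stated 80%.
- Two-sided 5%: Φ(2.472 − 1.960) = 69.6% (76.6% if 0.27% is the control risk).
- Full 1:4 matching, two-sided: about 86% to 88%, with a detectable ratio of about 1.16.

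The sidedness of the test is a separate matter. For this point, 1.18 serves only as a scale for the bias.

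**2. Is the marker used in a melanoma model?** The Confounding subsection lists four covariates and four matching variables, none of them solar keratosis. The changes section reports no alteration to that set. Of its four additions, only items 3 and 4 mention solar keratosis, once as an outcome and once in relation to exposure. No adjusted, restricted or stratified melanoma analysis using it is described.

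**3. How large could UV bias be?** With a true hazard ratio of 1, the spurious ratio is

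(1 + p1(g − 1)) / (1 + p0(g − 1)),

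where g is the melanoma rate ratio for high versus low sun, and p1 and p0 are the proportions of high-sun men among exposed and controls. All three are assumptions; the documents give none of them. Where an odds ratio is assumed, p1 follows from it: for example 0.3/0.7 × 1.3 = 0.557, and 0.557/1.557 = 0.358.

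| g | p0 | p1 | Odds ratio, UV–PDE5 | Spurious hazard ratio |
|---|---|---|---|---|
| any | any | equal to p0 | 1.0 | 1.00 |
| 2 | 30% | 35.8% | 1.3 | 1.358/1.300 = 1.044 |
| 3 | 40% | 50% | 1.5 | 2.00/1.80 = 1.111 |
| 5 | 30% | 39.1% | 1.5 | 2.565/2.20 = 1.166 |
| 3 | 40% | 55% | 1.83 | 2.10/1.80 = 1.167 |
| 4 | 40% | 55% | 1.83 | 2.65/2.20 = 1.205 |

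**4. How much would adjustment remove?** Take the second row (g = 2, 35.8% v 30%, biased ratio 1.044) and 1:4 matching. Replace true UV status with a yes/no marker of assumed sensitivity and specificity, and combine the two marker strata by Mantel–Haenszel.

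For sensitivity 50% and specificity 95%, per exposed man:

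- Marker positive: exposed 0.2110 with relative events 0.3899; controls 0.740 with 1.340.
- Marker negative: exposed 0.7890 with 0.9679; controls 3.260 with 3.860.
- Numerator: 0.3899 × 0.740/0.951 + 0.9679 × 3.260/4.049 = 1.0827.
- Denominator: 1.340 × 0.2110/0.951 + 3.860 × 0.7890/4.049 = 1.0495.
- Adjusted ratio: 1.0827/1.0495 = 1.032.

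| Sensitivity | Specificity | Adjusted ratio | Share of log bias removed |
|---|---|---|---|
| 10% | 98% | 1.043 | 3% |
| 20% | 98% | 1.040 | 10% |
| 30% | 97% | 1.037 | 16% |
| 50% | 95% | 1.032 | 28% |

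These figures assume that recording errors do not depend on exposure or on melanoma. Recording that depends on consulting would break that assumption.

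**The case against.** A reader might infer that the main hazard ratio is in fact confounded by UV and cannot be interpreted. The documents do not support that. Confounding needs UV to be associated with PDE5 use within matched sets, and the Limitations section calls this unclear. Item 4 says only that the association was examined. Item 2 mentions an apparent role for sun exposure, which is suggestive but does not establish a link with PDE5 use. Nor does a diagnosis code for solar keratosis contradict the statement that UV data are unavailable: it is an indirect marker, not a measurement.

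The investigators also did a good deal about UV: practice matching carried through to a stratified model, deprivation score, negative control outcomes that include two skin conditions, interaction by region, and an open statement of the remaining gap. These deserve credit as partial control and as bias detection.

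The larger bias figures need strong inputs. Reaching 1.17 to 1.20 from a 55% v 40% split means an odds ratio of 1.83 (0.55/0.45 ÷ 0.40/0.60) after matching and adjustment, together with a three- to fourfold melanoma rate ratio. The milder 50% v 40% case reaches only 1.11. The 1.18 is a detectable effect, not an observed one.

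All of this stands, and so does the limited power of the remedy shown above. What it does not answer is that the marker was available, that the investigators chose it as a sun-exposure proxy, and that no described analysis shows the melanoma hazard ratio with it taken into account.

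**Conclusion.** Residual UV confounding is possible despite practice matching and adjustment for deprivation, and the described analyses leave unused, in the melanoma models, a patient-level proxy that would help to gauge it. This is a cheap and worthwhile improvement, not a demonstrated flaw in the primary estimate.

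The illustrative spurious hazard ratio runs from 1.00, if PDE5 use is unrelated to UV, to about 1.20. Every input to that range is assumed.

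The absence is judged from a short summary of changes, so the exact statement is that no such model is described. One may have been run without being listed.

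**What to change.** Keep the pre-specified hazard ratio as primary. Add two sensitivity analyses, labelled post hoc:

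1. The adjusted Cox model, stratified by matched set, with solar keratosis recorded on or before the index date (yes/no) added.
2. The melanoma analysis restricted to men without solar keratosis recorded on or before the index date.

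Add the same covariate to the basal cell carcinoma and colorectal cancer negative-control models. Where solar keratosis is itself the outcome, exclude men with prior disease instead of adjusting for it. Report these results beside the primary hazard ratio, together with the result of item 4. If such a model was already run, say so.

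The cost is one covariate already extracted and a few extra model runs; the restricted run will also lose some matched sets. Solar keratosis is incompletely recorded and depends on consulting and skin examination. Excluding men with no consultation in the prior year reduces that problem only partly. The text should therefore state that adjustment removes only part of any UV bias and that a small change does not exclude UV confounding. It should also say that the change is not a lower bound on that confounding, because it may partly reflect surveillance.
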